## Methods

### Ethical Considerations

A waiver of consent was granted for this study by the institutional ethics committee (St Vincent’s Hospital Melbourne human research ethics committee project ID 81922, Local Reference LRR 315/21).

### Study Methodology

#### Study Design

A pilot, prospective, single-arm, intervention approach was followed for this study.

#### Study Setting

This study was conducted at the FibroScan clinic of a single tertiary center linked to a large pathology service, which provides both public and privately funded pathology services for the general population in regional and urban areas of Victoria, Australia.

### Primary Outcome Measurement

The primary outcomes prospectively commenced on August 1, 2023, for 6 months before intervention and will continue until the conclusion of the intervention period on July 31, 2024. The impact of the intervention will be determined by comparing primary outcome measures during the intervention period to the 6 months prior to the intervention (standard of care).

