### Recruitment

All individuals aged 18 years and older who have liver function tests and full blood count requested by a community-based health worker and performed at St Vincent’s Pathology between August 1, 2023, and July 31, 2024, will be recruited. There will be no active recruitment of participants for this study.

This study is an evaluation of a health system–wide introduction of routine reporting of APRI calculation, information on liver cirrhosis, and a web link through St Vincent’s Pathology to improve the quality of care for people with liver disease; therefore, no individuals will individually consent to participate. No personally identifying information will be collected and all data supplied to the research team will be deidentified by St Vincent’s Pathology and transient elastography booking and reporting teams, respectively. Variables including 10-year age category, sex, and postcode will be collected as part of the study but will not allow identification of individuals, as they are broad categories expected to contain more than 1000 persons per strata per month during the study period.

The exclusion criteria of this study include children aged 18 years or younger and blood tests performed during a hospital inpatient stay, or requested by hospital outpatient service, defined by St Vincent’s Pathology records (blood collection site).

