### Study Timeline

#### Preintervention Period

Between August 1, 2023, and January 31, 2024, St Vincent’s Pathology will prospectively collect data on all ALT, AST, and platelet count test results conducted, and APRI and FIB-4 scores will be automatically calculated by the St Vincent’s Pathology data management system, but not reported to the ordering clinician. These data will be prospectively collected from St Vincent’s Pathology by a member of the study team, along with exposure variables outlined above. During the same time period, outcome measures per month will be prospectively collected from the St Vincent’s hospital electronic medical records by a member of the research team (number of FibroScan referrals, number [proportion] of scheduled FibroScan appointments attended, number [proportion] diagnosed with cirrhosis, and number [proportion] linked to specialist care).

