#### Intervention Period

From February 1, 2024, to July 31, 2024, St Vincent’s Pathology will commence inclusion of automatic calculation of APRI and FIB-4 score reporting on all pathology blood testing events where an AST, ALT, and platelet count are ordered. St Vincent’s Pathology will provide for these testing events: (1) the APRI result, (2) the FIB-4 result, (3) an explanation of what APRI and FIB-4 measure and what cutoffs are used to define cirrhosis, and (4) recommendations for further investigation of elevated APRI or FIB-4 with transient elastography (FibroScan) and performance of a liver disease screen if underlying liver disease is not known. In addition, a web link to the St Vincent’s Pathology website for liver disease and cirrhosis information page will be included on all blood test reports where APRI and FIB-4 are calculated, with a provided URL link to a unique St Vincent’s Hospital FibroScan referral form. This link will be distinct from the standard fax-based St Vincent’s FibroScan referral form to allow measurement of referrals specifically generated in response to St Vincent’s Pathology APRI or FIB-4 score calculations during the study period.

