### Statistical Analysis Plan

#### Outcome Measures

Data will be analyzed per test event and per individual tested.

Primary outcomes of this study include the number of APRI and FIB-4 scores calculated on blood test events conducted during the study period, overall and per month; the number (proportion) of APRI scores that are greater than 1.0 and FIB-4 scores that are greater than 2.67; number of FibroScan referrals overall and per month, operationalized as number of completed FibroScan referrals generated online using the recommended St Vincent’s Pathology FibroScan referral link on the request slip, or St Vincent’s Pathology APRI or FIB-4 calculation web page referral form link; number of individuals with an APRI greater than 1.0 or FIB-4 score greater than 2.67 who undergo a FibroScan test at St Vincent’s Hospital Melbourne overall and per month; proportion of individuals with an APRI greater than 1.0 or FIB-4 score greater than 2.67 who undergo a FibroScan test at St Vincent’s Hospital Melbourne; the number of individuals per month who undergo FibroScan at St Vincent’s Hospital Melbourne who have cirrhosis diagnosed (liver stiffness measurement >12.5kPa); the number (proportion) of individuals with an APRI greater than 1.0 or FIB-4 score greater than 2.67 who have cirrhosis confirmed by FibroScan; the number (proportion) of individuals with etiology-specific cirrhosis range FibroScan results that are referred to the specialist liver clinic; and the number (proportion) of individuals with etiology-specific cirrhosis range FibroScan results that attend to the specialist liver clinic appointment.

The secondary outcomes of this study include the number (proportion) of individuals, stratified by age category, sex, and postcode who have elevated APRI greater than 1.0 and FIB-4 score greater than 2.67, attend the FibroScan clinic for further testing, have etiology-specific cirrhosis range FibroScan scores (kPa), and attend a liver specialist clinic appointment.

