## Results

As of January 2024, in the preintervention phase of this study, a total of 120,972 tests were performed by the laboratory. Of these tests, 78,947 (65.3%) tests were excluded, with the remaining 42,025 (34.7%) tests on 37,872 individuals meeting inclusion criteria with APRI and FIB-4 being able to be calculated (Figure 1). Of these, 1.3% (n=531) had elevated APRI greater than 1 occurring in 446 individuals, and 2.3% (n=985) had elevated FIB-4 greater than 2.67 occurring in 816 individuals (Table 1). Linking these data with FibroScan referral and appointment attendance is ongoing and will continue during the intervention phase.

Data analysis is expected to begin following 6 months of intervention in August 2024, and the publication of results will then follow.

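### Inclusion and outcome collection both end on July 31, 2024, so scans, diagnoses and clinic visits after late intervention tests are cut off, and the effect on the pre-post comparison depends on an unsettled counting rule

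*Protocol article*

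**What the plan says.** Under Recruitment, adults with an eligible community blood test "between August 1, 2023, and July 31, 2024, will be recruited". Under Primary Outcome Measurement, outcome collection started on August 1, 2023 and "will continue until the conclusion of the intervention period on July 31, 2024". The Results section adds: "Data analysis is expected to begin following 6 months of intervention in August 2024". The article states no run-out period and no follow-up window per person.

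Outcome Measures lists a sequence of primary outcomes. It begins with scores calculated and ends with the number and proportion of people with cirrhosis-range results "that attend to the specialist liver clinic appointment". The Intervention section says that the study schedules no tests or appointments beyond standard care, so usual-care delays apply.

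Three sections bear on how an event after the end of a phase is counted:

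- Primary Outcome Measurement compares the intervention period with the preceding 6 months, and gives one end date for outcome collection.
- Preintervention Period covers tests "Between August 1, 2023, and January 31, 2024" and continues: "During the same time period, outcome measures per month will be prospectively collected". This suggests that preintervention outcomes close on January 31, 2024.
- Results says of the preintervention tests: "Linking these data with FibroScan referral and appointment attendance is ongoing and will continue during the intervention phase". This suggests that their later events may still be counted after February 1, 2024.

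**The concern.** A person tested in late July 2024 can hardly be referred, scanned, diagnosed and seen in clinic by July 31. The shortfall is small for referral and grows with each step. It is largest for specialist attendance, and linkage to specialist care is half of the stated hypothesis.

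The comparison between phases is also at stake. A preintervention test may have 6 to 12 months for its events to be seen, or only the rest of its own phase, depending on which section is followed. The same records could then give a ratio that is too low, about right, or too high.

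**Working it through.** **Inputs.** Preintervention phase: August 1, 2023 to January 31, 2024. Intervention phase: "From February 1, 2024, to July 31, 2024". Both dates come from Study Timeline. The common end date comes from Primary Outcome Measurement and Recruitment. The documents give no delay from test to event, so the lags below are assumptions shown as a range. A constant daily number of tests is also assumed.

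**The plan's own figures.** The phases last 184 and 182 days, which agrees with the stated 6 months each. The plan gives no figure for completeness of follow-up.

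**Time from test to July 31, 2024.**

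- Intervention tests: 0 to 181 days, mean (0 + 181)/2 = 90.5. Under 30 days: 30/182 = 16.5%. Under 60: 60/182 = 33.0%. Under 90: 90/182 = 49.5%.
- Preintervention tests: 182 to 365 days, mean (182 + 365)/2 = 273.5. None has under 90 days.

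**Share of eventual events seen.** For an exponential lag with mean m, a test with x days of follow-up contributes 1 − exp(−x/m), averaged over test days. Let a be preintervention tests followed to July 31, b preintervention tests followed to January 31, and c intervention tests followed to July 31.

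| Mean lag (days) | a | b | c | (i) c/a | (ii) c/b | (iii) 1 + c |
|---|---|---|---|---|---|---|
| 30 | 1.000 | 0.835 | 0.833 | 0.833 | 0.998 | 1.83 |
| 60 | 0.985 | 0.687 | 0.684 | 0.694 | 0.996 | 1.68 |
| 90 | 0.943 | 0.572 | 0.569 | 0.603 | 0.994 | 1.57 |
| 120 | 0.887 | 0.486 | 0.483 | 0.545 | 0.993 | 1.48 |

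**(i) Test cohorts, one July 31 cut-off.** With no true effect the apparent ratio is c/a, from 0.833 down to 0.545. A fixed lag gives the same picture: at 30, 60, 90 and 120 days, 83.5%, 67.0%, 50.5% and 34.1% of intervention events are seen, against 100% in the preintervention phase.

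**(ii) Test and event in the same phase.** The ratio c/b stays within 1% of 1. The loss is still heavy: at a fixed 90-day lag, 51.1% and 50.5% of events are seen.

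**(iii) Events counted in the calendar month in which they occur, steady state before the study.** Under no effect there is no bias. If the true probability doubles from February 1, the apparent ratio is 1 + (2 − 1)c, that is 1.83 down to 1.48.

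**(iv) As (iii), for outcomes restricted to score-positive people, if no scores exist before August 2023.** The Comparator Group section says scores are calculated from the start of the study. The preintervention months would then hold no events from earlier tests, while the intervention months would hold events from preintervention tests. Under no effect the ratio of phase totals is [184(a − b) + 182c]/(184b). At a 30-day mean lag this is (30.4 + 151.6)/153.6 = 1.18. At 60, 90 and 120 days it is 1.42, 1.63 and 1.81.

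**The case against.** The strongest reply is that the phases are treated alike. Preintervention Period collects outcomes in the same period as the tests, and the abstract compares monthly rates over 6 months on each side. On that reading the truncation is almost equal, as (ii) shows. The Results sentence on linkage may mean only that the linking work goes on, not that preintervention people are followed to July 31. This stands. A reader might infer that the plan truncates the two phases unequally, or that it is biased against the intervention. The documents do not establish either, because both follow only from reading (i).

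It can also be said that event-attribution rules are commonly left to a full protocol or SAP that is not shown. That is fair for the rule itself. It does not cover the common end date, which the article states outright.

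Finally, this is a pilot with a feasibility aim. Score counts and the proportion elevated are unaffected, referral counts have the shortest lag, and an August start is only expected, not a stated data lock. All of this stands and limits the severity. It does not restore the scans, diagnoses and clinic visits that fall after July 31.

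**Conclusion.** The plan leaves intervention-phase tests a mean of 90.5 days, and a third of them under 60 days, for a multi-step chain under usual-care delays. The loss of downstream events follows from the stated dates. To say that late-tested people have no time at all would be literal only for the last days.

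The distortion of the comparison is conditional. It is about 0.833 to 0.545 under no effect with one cut-off for both cohorts, and negligible if each phase closes on its own last day. With calendar counts a true doubling is diluted to 1.83 to 1.48. Score-positive outcomes without carry-in show a spurious rise of 1.18 to 1.81. These figures rest on even testing, exponential mean lags of 30 to 120 days and equal lags in both phases, none of which the documents supply. Severity is moderate; the remedy is a cheap improvement.

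**What to change.** For FibroScan performed, cirrhosis confirmed and linkage to care:

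1. Assign each person to the phase of their first elevated test.
2. Count events within one equal, pre-specified window in both phases, for example 90 days. With no effect and equal delays, the capture ratio is then 1.00.
3. Extend the passive hospital-record extraction past July 31, 2024 by that window. For 90 days this is October 29, 2024. If July 31 were kept, only 92 of 182 intervention test days (50.5%) would have 90 days of follow-up.
4. Use a longer window for clinic attendance as a sensitivity analysis.
5. Flag preintervention people retested after February 1, 2024 in a sensitivity analysis. Censoring them at retest would make the windows unequal again.
6. Reconcile Primary Outcome Measurement, Preintervention Period and Results on how events after the end of a phase are attributed.

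Referral counts can stay on the August 2024 timetable.

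The cost is a data cut a few months later for the downstream outcomes and one more extraction, with no new participants or visits. Some preintervention windows will overlap the live intervention: 90 of 184 test days (48.9%) with a 90-day window. That is a reason not to make the main window much longer, since at 180 days it would be 180 of 184 (97.8%).

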### Definitions

#### Comparator Group (Standard of Care)

Currently, APRI and FIB-4 scores are not routinely reported anywhere in Australia. Prior to the intervention, blood tests will be reported per standard of care. APRI and FIB-4 scores will be calculated automatically by the pathology service from the start of the study but will not be reported to ordering clinicians until the intervention period. FibroScans are requested through a paper-based referral form by general practitioners or specialists, which is then faxed to the hospital for triage and booking.

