### Objectives

The primary objectives of this study are given below.

First, this study aims to measure the monthly rate and the number (proportion) of individuals with APRI greater than 1.0 and FIB-4 greater than 2.67 among people who undergo automated APRI and FIB-4 calculation on blood test events performed through a single Australian pathology service.

Second, this study aims to measure the monthly rate of transient elastography referrals received after the introduction of automated APRI and FIB-4 reporting, compared with the preintervention period.

Third, this study aims to measure the monthly rate and the number (proportion) of transient elastography tests performed in those with an elevated APRI and or FIB-4 score during the intervention period, compared with the preintervention period.

Fourth, this study aims to measure the monthly rate and the number (proportion) of individuals with APRI greater than 1.0 or FIB-4 greater than 2.67 that have cirrhosis range median stiffness (kPa) confirmed on FibroScan.

Finally, this study aims to measure the number (proportion) of individuals with cirrhosis range FibroScan during the intervention period that is linked to specialist care, compared with the preintervention period.

The secondary objective of this study is to describe the sociodemographic factors associated with (1) APRI greater than 1.0 and FIB-4 greater than 2.67, (2) attendance at FibroScan appointment, (3) cirrhosis diagnosed on FibroScan, and (4) linkage to specialist care.

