### Sample Size Justification

We have conducted a preliminary analysis of the number of AST and platelet count testing events that were performed at St Vincent’s Pathology over a 12-month period (2019). These data showed approximately 11,000 people known to St Vincent’s hospital clinics, and a further 4400 people in the community that had AST and platelet count testing events, that would have allowed APRI calculation to be performed, proving the feasibility of reaching large numbers within the community for cirrhosis screening.

For the comparison of rate of referral for FibroScan before and after the intervention, we estimate that we will be powered to detect a 10% difference in rates of FibroScan referral before and after the intervention. For the logistic regression analyses to determine the difference in proportion of APRI scores leading to referral before and after providing cirrhosis information and FibroScan referral link information (overall and by subgroup), and for determining the proportion of FibroScan referrals that are attended (overall and by subgroup), we are powered to detect a 5% or greater difference between the intervention and historical control groups with power 90% and a sample size of 1100 per subgroup. The above numbers of more than 15,400 individuals having APRI calculations within 12 months suggest that we will be adequately powered to explore our end points including stratified by sex, urban versus rural place of residence, age category, socioeconomic quartile of place of residence, and indication for FibroScan (all of which are expected to have >1000 individuals in each subgroup).

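### Scores and scan counts both start on August 1, 2023 with no lead-in and no score-to-scan rule, so counts of elevated-score people scanned are not comparable between phases

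*Protocol article*

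**What the plan says.** **Start of scores.** Under Comparator Group, "APRI and FIB-4 scores will be calculated automatically by the pathology service from the start of the study", though they are not shown to clinicians until the intervention begins. Under Recruitment, the people included are those with tests "performed at St Vincent’s Pathology between August 1, 2023, and July 31, 2024, will be recruited". This is one continuous window, with nothing before August 2023 and no reset at February 1, 2024.

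**Start of counting.** Under Primary Outcome Measurement, "The primary outcomes prospectively commenced on August 1, 2023, for 6 months before intervention". The same section judges impact by setting the intervention period against those six months. Under Preintervention Period, "During the same time period, outcome measures per month will be prospectively collected", that is, over the same calendar window as the blood tests.

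**What is counted.** The third primary objective is "the monthly rate and the number (proportion) of transient elastography tests performed in those with an elevated APRI and or FIB-4 score", intervention against preintervention. The matching primary outcome under Outcome Measures is the number of people with an elevated APRI or FIB-4 "who undergo a FibroScan test at St Vincent’s Hospital Melbourne overall and per month".

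**How it is analysed.** Analysis Methods gives a time-series analysis for referrals and linear regression for attendance.

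**Linkage.** Results reports 446 people with elevated APRI and 816 with elevated FIB-4 in the preintervention phase. It adds that linking these data to referrals and attendance carries on through the intervention phase.

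**The concern.** A scan can count as a scan in an elevated-score person only if an elevated result is on record. For a scan on August 10, 2023, the record goes back ten days at most. For a scan on February 10, 2024, it goes back more than six months. The same outcome is therefore ascertained with unequal look-back in the two phases.

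There are two consequences on a plain calendar count. Early preintervention scans that followed a June or July 2023 test are missed. Some intervention-phase scans will follow a December or January test whose score no clinician saw, yet they would count towards the intervention. A change between phases could then appear, or a real one be masked, whatever reporting does. The third objective would not be answered.

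**Working it through.** The document gives no figure for the test-to-scan lag or for carry-over, so there is no planned figure to reproduce. The check asks what the count would do if reporting had no effect.

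**Inputs from the document.** Scores and counting both start at month 0 (August 1, 2023). The interruption is at month 6 and the end is at month 12. There are 816 people with elevated FIB-4 and 446 with elevated APRI in the first phase.

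**Assumptions.** Elevated tests arrive at a constant rate, the lag from test to scan is exponential with mean m months, and status carries forward across February 1, 2024.

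**Formula.** The share of steady-state scans at time t whose qualifying test fell on or after month 0 is F(t) = 1 − exp(−t/m). In units of one steady-state month of scans:

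- preintervention = 6 − m(1 − exp(−6/m))
- intervention = [12 − m(1 − exp(−12/m))] − preintervention

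For m = 2, preintervention = 6 − 2(1 − 0.0498) = 4.10. The 12-month total = 12 − 2(1 − 0.0025) = 10.00, so intervention = 5.91 (from unrounded values) and the ratio is 1.44.

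| Mean lag (months) | Preintervention | Intervention | No-effect ratio |
|---|---|---|---|
| 0.25 | 5.75 | 6.00 | 1.04 |
| 0.5 | 5.50 | 6.00 | 1.09 |
| 1 | 5.00 | 6.00 | 1.20 |
| 2 | 4.10 | 5.91 | 1.44 |
| 3 | 3.41 | 5.65 | 1.66 |

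**Ramp at m = 2.** Monthly counts as a share of steady state are 0.21, 0.52, 0.71, 0.82, 0.89 and 0.94 before the intervention, then 0.96 to 1.00.

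**Carry-over at m = 2.** Intervention-phase scans with a same-phase test amount to 4.10, by the same integral. The rest follow unreported scores: (5.91 − 4.10)/5.91, or about 30%.

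**Other rules on the same no-effect series, m = 2:**

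- A 3-month score-to-scan window without a lead-in gives 4.66/3.78 = 1.23.
- Attribution by blood-test date, with scans counted to July 31, 2024, gives 4.10/5.91 = 0.69.
- A segmented regression with a preintervention trend gives a level change of −0.13 and a slope change of −0.13 per month, in steady-state units. The ramp is read as a trend and projected forward.
- Score and scan in the same phase gives 4.10/4.10 = 1.00.

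**What a test would see.** Suppose 816 elevated people per phase, 10% of them ever scanned (an assumption) and m = 2. The steady rate is 816 × 0.10/6 = 13.6 scans a month, so the expected counts are 13.6 × 4.10 = 56 and 13.6 × 5.91 = 80. A simple two-period comparison has expected z = (80.3 − 55.8)/√(80.3 + 55.8), about 2.1. It would reject a true null about 56% of the time at the two-sided 0.05 level.

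**The case against.** **The plan does not say that scores carry over.** This is correct. No passage states that a preintervention score qualifies an intervention-phase scan, and the third objective can be read as dating the score, not the scan. On that reading with same-phase pairing, nothing is biased. However, no passage limits a scan to a same-phase score either, the recruitment window is continuous, and linkage of the preintervention data is said to continue. The rule is open, and the stated dates make the choice consequential.

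**A reader might infer a spurious rise by construction, from a count that starts at zero.** The documents do not support that. The direction depends on the attribution rule and the model, as the ratios of 0.69, 1.00 and 1.44 and the negative segmented estimates show. The first month would be low, not empty. At lags of one to two weeks the distortion is only 4% to 9%.

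**The lag is assumed, and repeat testing softens the effect.** Both points stand. The 816 people with elevated FIB-4 had 985 elevated tests, and the 446 with elevated APRI had 531. Someone elevated in June and retested in August enters the record, which the model ignores. Still, standard care involves a faxed referral, triage and booking, so some lag is inherent.

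**The scope is limited.** This stands too. Total referrals, and cirrhosis found among all people scanned, do not depend on score status. The 10% difference in the sample size section concerns referral rates and is no yardstick here. The fourth objective states no comparison between phases.

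**Linkage detail may sit in the full protocol.** It may. But no later analysis rule can supply scores from before August 2023 unless the data window is widened.

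**Conclusion.** The point holds for the score-conditioned outcomes: the third objective and the matching counts of elevated-score people scanned. Because score ascertainment and outcome counting begin on the same day, a plain six-against-six-month calendar count has a ramp-up in the first phase only, and it includes intervention-phase scans that follow unreported scores. With no true effect, the ratio would be 1.04 to 1.09 at mean lags of one to two weeks, 1.2 at one month and 1.4 at two months. This rests on constant arrivals, an exponential lag and carried-forward status. The actual size cannot be derived, because neither the lag nor the proportion scanned is given. A segmented model on the same series would err in the opposite direction. The rule therefore needs to be fixed before analysis, which the article places in August 2024.

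**What to change.** Apply one score-to-scan window equally in both phases and state it before analysis.

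**Simplest: same-phase pairing.** Count a scan only if its qualifying elevated score fell in the same six-month phase and within a fixed window before the scan. This needs no new data and gives a no-effect ratio of 1.00. The cost is that scans following tests late in a phase are lost, equally in both phases. Under the model above, that is 1 − 5.00/6 = 17% of steady-state scans at a one-month mean lag and 1 − 4.10/6 = 32% at two months.

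**Alternative: scan date with equal look-back.** Count by scan date with the same fixed look-back in both phases, using scores computed retrospectively from stored February to July 2023 results. Report separately the intervention-phase scans that follow unreported preintervention scores. The cost is one laboratory extraction and possibly an ethics amendment for the wider data window. The preliminary 2019 analysis of "the number of AST and platelet count testing events that were performed" suggests that retrieval is feasible, although it describes no linkage to scans.

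**If scans are attributed by blood-test date,** give tests in both phases the same fixed follow-up. Otherwise truncation at July 31, 2024 biases the comparison the other way (0.69 at a two-month mean lag).

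None of these options adds patients or procedures.
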